### Eligibility criteria

Participants will be recruited from Hammersmith Hospital, Imperial College Healthcare NHS Trust. Patients will be provided with a verbal and written explanation of the trial and given the opportunity to discuss all aspects of the trial with both the clinician and research nurse. Patients who provide written consent to participate in the trial after at least 24 hours of consideration will be registered and therefore eligible to proceed to further assessment.

To be eligible, patients must have a radiological or histological diagnosis of HCC not amendable to any curative options including transplant, surgery or radiofrequency ablation. Patients with up to Child Pugh B7 liver function and liver dominant disease will be enrolled. Detailed inclusion and exclusion criteria are outlined in online supplemental table 1.

### Study procedures

Patients will undergo baseline tumour imaging including chest, abdominal and pelvic CT scan and MRI scan of the liver at screening (table 1). Up to 4 weeks following consent, patients will undergo angiography of the hepatic artery to assess the presence of aberrant vessels arising from hepatic arteries. If present, protective coiling of any extrahepatic branch (eg, aberrant segment IV and right gastric artery) will be undertaken. In the same session, a scout dose of maximum 250 MBq ^166^Ho-labelled microspheres, QuiremScout (Terumo Europe), will be injected into the hepatic artery via the same catheter position chosen for the scheduled RE session in order to calculate the hepatopulmonary shunt fraction. In cases of selective treatments, less activity will be injected for the scout, proportionally to the volume treated. Tracer distribution will be evaluated using [^166^Ho]Ho SPECT imaging. Following completion of the angiogram and scout imaging, a decision will be made regarding the dose to be delivered. The individualised treatment plan will attempt to optimise doses to achieve at least a tumour dose of 150 Gy while keeping normal liver doses to 45–60 Gy or lower. QuiremSpheres (Terumo Europe) will be administered up to 2 weeks following these investigations.

**Table 1 T1:** Treatment schedule

Procedures	Screening		Treatment	follow-up			
	Screening	Scout		W3	W6	M3	M6
Informed consent	X						
Inclusion/exclusion criteria	X	X	X				
Demographics	X						
Physical exam and clinical performance status (ECOG)	X					X	X
EORTC QLQ C30+HCC18	X					X	X
CT scan^*^	X						
MRI scan^†^	X		X			X	X
Tumour assessments (mRECIST)	X					X	X
SPECT/CT		X	X^‡^				
Angiography		X	X				
Scout dose		X					
Therapeutic dose			X				
Blood tests	X	X	X	X^§^	X^§^	X^§^	X^§^
(S)AE’s+Con Med	X			X	X	X	X

* CT scan chest + pelvis

† MRI liver with hepatic biliary contrast

‡ 3-4 days after treatment

§ No coagulation blood tests required

ECOG, Eastern Cooperative Oncology Group; EORTC, European Organisation for Research and Treatment of Cancer; mRECIST, modified Response Evaluation Criteria in Solid Tumors; SPECT, single-photon emission computed tomography.

Patients will be admitted the day of the procedure and discharged the same day. In patients with bilobar disease, the first treatment will be administered to the lobe with the greatest tumour burden. Treatment of the contralateral lobe will be scheduled for 4–6 weeks after the first treatment. Following administration of QuiremSpheres, patients will receive standard of care post-RE treatment to prevent radiation-induced hepatitis and gastric complications: reducing dose of dexamethasone 8 mg daily for 1 week, 6 mg daily for the following week, 4 mg daily the week after that and 2 mg daily for 1 final week, proton pump inhibitor 60 mg daily and ursodeoxycholic acid 250 mg every night. A post-therapy SPECT will be performed 3–4 days after QuiremSpheres administration.

Patients will be reviewed in week 3, week 6 and on a 3 monthly basis for 6 months or until disease progression, withdrawal from the trial or death (whichever comes first). Blood tests will be performed at each visit for safety. Tumour imaging will be repeated 3-monthly post-RE for 6 months. The same method for assessment at baseline must then be used at all subsequent time points. mRECIST criteria will be used to determine patient response to treatment and ORR. QoL questionnaires (EORTC QLQ-C30) and EORTC HCC18 will be completed at baseline, and 3-monthly post-RE until trial completion.

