## Methods and analysis

### Trial objectives

The primary objective is to determine the incidence of adverse and serious adverse device events (ADEs/SADEs) overall and by severity, graded by the National Cancer Institute—Common Toxicity Criteria (NCI-CTC v5.0). The co-primary objective is to determine the objective response rate (ORR) with [^166^Ho]Ho-RE, defined as the rate of best overall response (which includes complete responses and partial responses) in the treated liver volume as determined by RECIST 1.1 and mRECIST. In addition, the total hepatic response and overall response will be assessed according to RECIST 1.1 and mRECIST.

The secondary objectives are quality of life (QoL) as determined using the European Organisation for Research and Treatment of Cancer (EORTC) questionnaires QLQ-C30 and HCC18 at baseline and every 3 months. Exploratory endpoints include the assessment of radiomics in the prediction of treatment response determined by CT scans of the liver at baseline, 12 weeks post RE and at disease progression. Biodistribution and dosimetry received to tumour and normal liver will be reported. The results of this study will be combined with the identical iHEPAR study.

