### Safety

All adverse events (AEs) and adverse reactions (ARs) will be reported in a timely fashion. AEs and ARs, whether expected or not, will be collected and recorded during clinical assessments at weeks 3 and 6 and 3-monthly for 6 months (NCI-CTC v5.0). When serious adverse events (SAEs) occur, an SAE form will be completed within 24 hours. The chief investigator will determine whether SAEs were ‘related’ (resulting from the administration of the study treatment or procedure) or ‘unexpected’ (an event not listed in the study protocol as an anticipated occurrence) and report this to the research ethics committee. Any questions concerning AE reporting will be directed to the chief investigator in the first instance. The chief investigator will notify the sponsor of all SAEs that occur.

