## Discussion

Personalised dosimetry is central to achieving clinical benefit in patients with HCC.^18^ Therapeutic delivery of [^90^Y]Y-labelled microspheres is routinely used in clinical practice, with [^99m^Tc]Tc-MAA used as a surrogate of dose distribution. The use of a surrogate has been shown to be inaccurate with regard to calculating the dose delivered to the tumour.^2 3^ As both a beta and gamma-emitter, [^166^Ho]Ho-labelled microspheres can be used for both dosimetry and for therapy, improving the accuracy of dose delivered. However, individualised treatment planning inherently leads to treatment doses that deviate from the currently approved ‘one-size-fits-all’ approach (ie, 60 Gy average absorbed dose in the perfused liver volume for all patients.^16^ Therefore, the safety of individualised ^166^Ho-RE needs to be evaluated especially in this patient group, the majority of whom have a background of chronic liver disease.

The results of this work will be combined with the identical iHEPAR study being conducted in the Netherlands, increasing the power of both studies and allowing validation of the technology across countries. Combined final analysis will allow determination of radiation safety thresholds. These thresholds will be used in subsequent randomised controlled studies of [^166^Ho]Ho-RE for HCC. The approach of using a harmonised protocol across countries reduces the costs of a multisite study while still maintaining the rigour needed to combine results across sites. Moreover, it allows sites in different countries to gain experience in a novel technology. RHEPaiR will also generate much needed local knowledge for regulatory approval within the UK. This trial will add prospective clinical outcomes to a space dominated by retrospective work particularly with regard to dosimetry, giving further support for the use of RE in HCC. Moreover, imaging biomarker work for the prediction of clinical outcome in particular radiomics will be studied, which may aid in treatment choice for patients moving forward.

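### Table 1 requires no coagulation test at any follow-up visit, so INR-based toxicity and a full Child-Pugh score are not systematically ascertained after treatment

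*Protocol article*

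**What the plan says.** Table 1 (Study procedures) schedules blood tests at all seven columns: screening, scout, treatment, W3, W6, M3 and M6. The last four carry footnote §: "No coagulation blood tests required". The text below the table adds: "Blood tests will be performed at each visit for safety". The article does not list the analytes.

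The table row that begins "Physical exam and clinical performance status (ECOG" is marked at screening, M3 and M6 only. The adverse event row is marked at screening and at all four follow-up visits. The Safety section says that adverse events and reactions are "collected and recorded during clinical assessments at weeks 3 and 6 and 3-monthly for 6 months (NCI-CTC v5.0").

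The primary objective is to "determine the incidence of adverse and serious adverse device events (ADEs/SADEs) overall and by severity". Under Eligibility criteria, "Patients with up to Child Pugh B7 liver function and liver dominant disease will be enrolled"; Child-Pugh appears nowhere else in the article. The Discussion says that safety needs evaluating especially in these patients, "the majority of whom have a background of chronic liver disease". It also states: "Combined final analysis will allow determination of radiation safety thresholds".

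**The concern.** The trial asks whether individually planned radiation to the liver is tolerable in patients whose livers are mostly already diseased. Its eligibility limit is a liver-function score that, in its usual form, includes a coagulation item. That item is then waived at every follow-up visit.

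This is not a detail that a condensed article leaves to the full protocol. It is an explicit waiver, and no later analysis plan can recover a value that was never measured.

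The problem is how an unmeasured event enters the result. If INR is not tested, a rise that causes no symptoms does not appear as a missing value. It appears as no event. The rule under Data collection that the primary endpoint is not imputed gives no protection, because nothing is flagged as missing. The error can only lower the count of coagulation-related toxicity or its grade. If INR is tested only on clinical suspicion, the patients tested are a selected group: a proportion among them is not the incidence in the treated population, and a proportion among all treated patients is a lower bound.

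**Working it through.** The article gives no figure on this point to reproduce. The check is a count of schedule marks, read beside the text.

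**1. Marks at the four follow-up visits (Table 1)**

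| Item | W3 | W6 | M3 | M6 | Total |
|---|---|---|---|---|---|
| Blood tests | yes | yes | yes | yes | 4 of 4 |
| Coagulation required | no | no | no | no | 0 of 4 |
| Adverse event recording | yes | yes | yes | yes | 4 of 4 |
| Physical examination/ECOG | no | no | yes | yes | 2 of 4 |

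**2. Baseline against follow-up.** Screening, scout and treatment bloods carry no waiver. A footnote that removes coagulation from the later draws implies that it belongs to the earlier ones. A baseline value should therefore exist, with no required later value to compare with it.

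**3. What depends on coagulation.** Two assumptions come from outside the article: that a rise in INR is a gradable item in the toxicity criteria used, and that Child-Pugh is the usual five-item score (bilirubin, albumin, INR or prothrombin time, ascites, encephalopathy). Under these, neither an INR grade nor a complete Child-Pugh score is assured at any of the four visits. The other four items are not touched by the footnote, but because the analytes are not listed, bilirubin and albumin can be taken neither as present nor as absent.

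**4. A possible exception.** In bilobar disease the second treatment follows the first by 4–6 weeks. Treatment-visit bloods carry no waiver. If that column also applies to the second session, which the article does not say, those patients would have one coagulation result after first exposure. Unilobar patients would have none.

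**5. Scale.** The Statistical analysis section plans 15 patients. If all 15 are treated, one patient wrongly counted as free of a given toxicity changes its incidence by 1/15 = 0.067, or 6.7 percentage points. This applies to a patient-level incidence, and only where the patient has no other event that already counts. It shows how sensitive the estimate is. It does not predict how many events would be missed, and the article offers no basis for such a prediction.

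**6. W3 and W6.** The Safety section describes clinical assessments at these visits and the adverse event row is marked there, but the physical examination row is not. The two places do not agree on what the visit contains.

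**The case against.** The strongest reply is that this is a monitoring choice in a small pilot, not an error, and that several stronger readings a reader might draw from Table 1 fail.

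- *That INR toxicity or Child-Pugh cannot be graded after treatment.* The documents do not support this. Not required is not prohibited. The Safety section has all adverse events recorded, expected or not, so an INR measured for clinical reasons can be graded. Ascertainment is unsystematic, not impossible.
- *That nobody looks for clinical decompensation before M3.* This rests on one row of the table. Patients are reviewed at W3 and W6, and adverse events are recorded and graded at all four visits, so ascites or encephalopathy can be reported at each. Only the mismatch over visit content remains.
- *That the trial loses its main liver-function outcome.* It names no such outcome. The primary endpoint covers all device-related events, many of which do not depend on INR, and Child-Pugh is only an entry limit. Nor does the Discussion say that synthetic liver function must be measured; it speaks of the safety of the treatment.
- *That the pooled safety thresholds are compromised.* The iHEPAR visit schedule is not shown. If iHEPAR has the same waiver, adding INR in these 15 patients would leave the pooled data incomplete; if it does not, the gap lies in this trial alone. The article does not settle which.

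All four limits stand. So does the observation that other liver tests may be in the panel, so that much hepatic toxicity could be detected without INR. None of this answers the remaining point: testing only on suspicion finds overt cases and tends to miss silent ones, and the primary endpoint is an incidence by severity.

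**Conclusion.** The point holds in a narrow form. Coagulation is required at 0 of 4 follow-up visits, so INR-based toxicity and a full Child-Pugh score are not systematically ascertained after treatment, with a possible single exception in bilobar patients. This weakens a primary endpoint of graded toxicity in a population selected on Child-Pugh and mostly with chronic liver disease. The direction is towards under-counting or under-grading. The amount cannot be estimated from the article; one misclassified patient among 15 is worth 6.7 percentage points.

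The conclusion assumes the five-item Child-Pugh score and that a rise in INR is gradable under the criteria used. It does not depend on which other analytes are in the panel. It is a cheap improvement to the measurement of the primary safety endpoint, not a contradiction that invalidates the design. The W3/W6 examination question is a separate matter of reconciliation.

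**What to change.** 1. In Table 1, remove the footnote § waiver for INR/prothrombin time at W3, W6, M3 and M6, so that it is measured from blood draws already scheduled.
2. In the safety analysis, summarise INR grade by visit descriptively and, where all components are available, Child-Pugh change from baseline. Neither needs to become a formal endpoint or carry a test. Report the number of patients with a value at each visit, so that untested patients are not read as event-free.
3. State whether the treatment-column blood tests also apply to a second session in bilobar disease.
4. Reconcile Table 1 with the Safety section on what the W3 and W6 clinical assessments contain.

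Cost: one extra tube per scheduled draw, at most 15 × 4 = 60 tubes if every patient completes one follow-up series, plus a short table in the report. No visit or venepuncture is added. Items 3 and 4 need only a sentence each. Results already missed in patients past a given visit cannot be recovered, so the report should give the date of the change and the number of patients followed before it.

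### Patient reviews end at disease progression, while adverse event recording, month-6 bloods and quality of life carry no such limit; if the review rule governs, the primary toxicity incidence may be biased downward

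*Protocol article*

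**What the plan says.** Trial objectives in the protocol article sets the primary endpoint: "The primary objective is to determine the incidence of adverse and serious adverse device events (ADEs/SADEs) overall and by severity". No time horizon is attached to it.

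Study procedures, after fixing reviews at weeks 3 and 6, continues them "on a 3 monthly basis for 6 months or until disease progression, withdrawal from the trial or death (whichever comes first". The same paragraph says "Blood tests will be performed at each visit for safety" and "Tumour imaging will be repeated 3-monthly post-RE for 6 months". It says of the two questionnaires that they "will be completed at baseline, and 3-monthly post-RE until trial completion". None of these last three sentences mentions progression.

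The Safety section says that adverse events and reactions "will be collected and recorded during clinical assessments at weeks 3 and 6 and 3-monthly for 6 months", again without a limit at progression. It gives serious events a separate route: "When serious adverse events (SAEs) occur, an SAE form will be completed within 24 hours".

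Table 1 marks adverse events, blood tests and questionnaires at both month 3 and month 6. Its footnotes cover scan type, the timing of the post-treatment SPECT/CT and coagulation tests; none concerns progression.

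Statistical analysis defines the safety set as all patients who received radioembolisation and reports frequencies of events. Data collection rules out imputation for the primary endpoint.

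**The concern.** Progression is an efficacy event. It does not undo exposure to a radiation dose that has already been given, so it is not a natural end to toxicity follow-up. The article itself notes in its Discussion that most of these patients have underlying chronic liver disease, and eligibility extends to Child-Pugh B7. It is plausible, though not shown in the document, that patients who progress are also more likely to have liver toxicity. A stop at progression would then be informative about the endpoint.

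All treated patients stay in the denominator, no allowance for unequal follow-up is stated, and missing primary data are not imputed. An event that is never recorded therefore counts as no event. This is a data-collection rule, so an analysis plan written later cannot recover what was not collected. The stake goes beyond this small trial: the Discussion says the pooled analysis with iHEPAR will be used to set radiation safety limits for later randomised studies, and under-recorded late toxicity would push those limits in the permissive direction.

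**Working it through.** **Step 1. Set the rules side by side for a patient who progresses at the month-3 scan.**

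| Item | Where stated | Stop at progression stated? | Tied to a visit? | Month-6 record if the review rule governs |
|---|---|---|---|---|
| Patient review | Study procedures | Yes | – | None |
| Adverse events | Safety; Table 1 | No | Yes, recorded at clinical assessments | None scheduled for non-serious events |
| Safety bloods | Study procedures; Table 1 | No | Yes | None scheduled |
| Serious adverse events | Safety | No | No, reported on occurrence | Route remains |
| Questionnaires | Study procedures; Table 1 | No, run to trial completion | Not stated | Unclear |
| Tumour imaging | Study procedures; Table 1 | No | Not stated | Unclear |

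The two readings give different month-6 data for the same patient, and the article does not say which applies.

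**Step 2. Locate the window at risk.** The first scheduled response imaging is at month 3, when adverse events and bloods are also due. A patient found to progress on schedule has week 3, week 6 and month 3 data and can lose only the month-6 visit. An earlier loss requires progression to be found off schedule. For bilobar disease the second treatment comes 4–6 weeks after the first. If visits are counted from the first treatment (the article does not say), month 3, at about 13 weeks, leaves 13 − 6 = 7 to 13 − 4 = 9 weeks of follow-up for the second lobe.

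**Step 3. Size on assumed inputs.** The article gives no figure for progression by month 3, for late toxicity or for their association, so there is no stated figure to reproduce on this point. The 85% power and 25% toxicity rate in Statistical analysis belong to iHEPAR and do not bear on it; 25% is borrowed below only as a convenient scale.

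Assumptions:
- true 6-month proportion of patients with toxicity, p = 0.25 (0.25 × 15 = 3.75 patients);
- share progressing at month 3, q = 0.20 to 0.40 (3 to 6 of 15);
- share of toxicity first arising after month 3, L = 0.10 to 0.50;
- late-toxicity risk ratio in progressors against non-progressors, k = 1 or 2;
- every late event in a progressor goes unrecorded (worst case).

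Late risk in non-progressors: b = pL / (1 − q + qk). Proportion of patients with a lost event: qkb. Observed rate: p − qkb.

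| q | L | k | b | Lost, qkb | Observed rate | Lost of 15 |
|---|---|---|---|---|---|---|
| 0.20 | 0.10 | 1 | 0.025 | 0.20 × 0.025 = 0.005 | 24.5% | 0.08 |
| 0.40 | 0.50 | 1 | 0.125 | 0.40 × 0.125 = 0.050 | 20.0% | 0.75 |
| 0.20 | 0.10 | 2 | 0.025/1.2 = 0.0208 | 0.40 × 0.0208 = 0.0083 | 24.2% | 0.12 |
| 0.40 | 0.50 | 2 | 0.125/1.4 = 0.0893 | 0.80 × 0.0893 = 0.0714 | 17.9% | 1.07 |

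The downward bias is 0.5 to 7.1 percentage points. If iHEPAR has the same stop rule, which is not shown, the expected loss in the pooled 45 patients is 0.23 to 2.25 at k = 1 and 0.38 to 3.21 at k = 2.

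**Step 4. Share of late events only.** The fraction of month 3–6 events missed is qk / (qk + 1 − q). It is 20–40% at k = 1. At k = 2 it is 0.4/1.2 = 33% to 0.8/1.4 = 57%. These are fractions of late events, not of all toxicity.

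**The case against.** The strongest reply is that nothing in the article says adverse event collection stops at progression. The Safety section, which is the natural authority, gives six months without that limit, and Table 1 agrees. A reader might infer from the review sentence that progressors contribute no safety data after month 3. The documents do not support that: it follows only if the review rule overrides the Safety section. Even then serious events, and so serious adverse device events, have a 24-hour route that needs no visit and has no stated end. Serious liver decompensation would come through it, provided the site learns of it. All of this stands.

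A reader might also take the 33–57% in the last step of the working as the share of toxicity missed. It is not. It covers months 3–6 only, needs a doubled risk in progressors, and assumes that no late event in them is recorded by any route. On the 6-month incidence the effect is much smaller and could be negligible. For scale, an exact 95% interval for 4 of 15 runs from about 8% to 55%, so sampling error in this trial dwarfs the bias. Nor can it be claimed that month-6 quality of life will be seen only in progression-free patients, since the questionnaire sentence runs to trial completion.

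Finally, this is a condensed article, and the full protocol may settle the matter. That limits how strongly the point can be put, but it does not remove it: the article does state a stop rule, and that rule does not agree with its own Safety section and table.

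**Conclusion.** The point holds as an unreconciled follow-up rule that may bias the primary endpoint. It is not a demonstrated under-count. If the review rule governs, non-serious adverse device events and visit-based laboratory toxicity after progression have no scheduled collection, mainly at month 6, and the crude incidence in all treated patients can only be lowered. If it does not govern, the review sentence is wrong as written. Either way the text needs changing.

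The size cannot be computed from the document. The range of near zero to about 7 percentage points rests entirely on the assumed rate, progression share, late share and risk ratio, and on the worst case that no late event in a progressor is recorded. What is firm is the direction of any bias, and that later analysis cannot repair it.

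**What to change.** Reconcile Study procedures, Table 1 and Safety so that only tumour-response follow-up may end at progression. State that adverse event and serious adverse event recording, safety bloods and quality of life continue to month 6, or to death or withdrawal of consent, regardless of progression. Record the start date of any next anticancer therapy, so that toxicity can be shown over the full six months and also censored at that date.

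The cost is a minor amendment and one further visit or contact, already in the schedule, for each patient who progresses. Some late events will be confounded by the next therapy, which the censored presentation makes visible but does not resolve. Because the results are to be pooled with iHEPAR, whose stop rule is not shown, check that the two trials collect toxicity over the same window before the change is made.
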